#### Secondary clinical outcomes

The C-SSRS is a clinician-administered measure used to evaluate suicide risk by assessing both suicidal ideation and suicidal behavior. Suicidal ideation is rated on a five-level severity scale (1–5), with higher ratings reflecting more severe and imminent risk. Suicidal behavior is documented as categorical events, including preparatory actions, aborted or interrupted attempts, and actual suicide attempts. The C-SSRS has demonstrated strong reliability, validity, and predictive value in clinical populations and is widely adopted as a primary outcome measure in suicide-focused research (33).

The BDI-II is a 21-item self-report measure assessing the core symptom domains of depression. Each item is rated on a 4-point scale (0–3), yielding a total score ranging from 0 to 63, with higher scores indicating more severe depressive symptoms. The BDI-II has demonstrated excellent internal consistency (Cronbach’s α ≈ 0.94) and robust psychometric validity, supporting its use as a reliable indicator of depressive symptom severity in clinical research (34).

### Neurophysiological mechanistic outcome

#### ERP measurement

The ERP data acquisition system comprises a BrainAmp Standard amplifier (Brain Products GmbH, Germany) coupled with a 64-channel EasyCap electrode cap (Brain Products GmbH, Germany). The recording electrodes are placed at Cz and Pz, as these sites typically exhibit the largest and most stable amplitudes of the P300 component. The averaged mastoid references (A1, A2) serve as the reference electrodes, while the ground electrode is positioned at the forehead (FPz). Horizontal electrooculogram (HEOG) electrodes are placed at the outer canthi of both eyes, and vertical electrooculogram (VEOG) electrodes are positioned below the left eye. Electrode-scalp impedance is maintained below 5 kΩ for all recording sites. Electrode placement follows the 10/20 system of the International Federation of Clinical Neurophysiology, with electrode resistance < 5 kΩ (35).

### P300 data acquisition

#### Participant preparation

The experiment will be conducted in an acoustically and electrically shielded chamber with soft ambient lighting. Room temperature will be maintained at 22–25 °C to ensure participant comfort. Measures will be taken to shield monitors and cables from 50 Hz power line interference. Participants will be instructed to abstain from consuming coffee, tea, alcohol, or other central nervous system−affecting substances for 24 h prior to the experiment and to obtain adequate rest to remain alert and relaxed. Before formal data acquisition, participants will sit quietly in the laboratory for 5–10 min to adapt to the experimental environment.

#### Task instructions

The experimenter will deliver standardized, concise verbal instructions to clearly explain the auditory oddball paradigm: “You will hear two different tones through the headphones. One tone occurs frequently (the ‘high−pitch tone’), while the other occurs infrequently (the ‘low−pitch tone’). Your task is to press the response button as quickly and accurately as possible when you hear the infrequent ‘low−pitch tone’, and to make no response to the frequent ‘high−pitch tone’. Please keep your head and body still and try to minimize eye blinks throughout the recording.”

#### Stimulus presentation parameters (classic auditory oddball paradigm)

The auditory stimuli will consist a standard tone (1000 Hz pure tone, 80 % probability) and a target tone (2000 Hz pure tone, 20 % probability). Both tones will be presented binaurally at 75 dB SPL with a duration of 50–100 ms. The inter−stimulus interval will vary randomly between 1.0 and 1.5 s (36).

#### Data acquisition procedure

Before the formal experiment, participants will complete a short practice session (approximately 20–30 trials) to ensure full comprehension of the task and accurate discrimination between the two sounds. Practice data will not be included in the formal analysis.

#### Formal acquisition

(1) EEG recording will be started. (2) Participants will sit upright in front of the screen (optionally fixating on a “+” cross−hair at the center of the screen to reduce eye movements), wear headphones, and place their hands on the keyboard. (3) The program will automatically and randomly present standard and target stimuli. (4) E−Prime 3.0 software and the EEG recorder will be activated to synchronously record stimulus markers, EEG signals, and button−press responses. (5) The acquisition will last approximately 3 minutes. The specific operational procedure is shown in **Figure 3**.

**Figure 3 f3:**
[figure not shown]
Experimental setup and paradigm for P300 assessment via EEG panel; **(a)** depicts the EEG recording setup, where a participant undergoes electrode placement with a 64-channel EEG cap, while synchronized stimulus presentation and data acquisition are managed by dedicated software. **(b)** illustrates the electrode montage following the extended 10–20 system, with “L” and “R” indicating left and right hemispheres, enabling high-resolution cortical activity monitoring. **(c)** outlines the auditory oddball paradigm used to elicit P300: two types of sounds (high-pitched, 80% probability; low-pitched, 20% probability) are presented randomly, with a stimulus duration of 50–100 ms, inter-stimulus interval of 1.0–1.5 s, and total task duration of 3 minutes. This paradigm is designed to assess attentional resource allocation and information processing efficiency, indexed by P300 latency and amplitude.

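### The pitch of the rare target tone in the P300 task is contradictory: the stimulus settings make it the higher tone, the participant script and Figure 3 legend make it the lower one

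*Protocol article*

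**What the plan says.** Three places in the protocol article describe the two tones of the auditory oddball task.

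- **Stimulus presentation parameters** gives the tone frequencies: "standard tone (1000 Hz pure tone, 80 % probability") and "target tone (2000 Hz pure tone, 20 % probability"). The lower tone is common and the higher tone is the rare target.
- **Task instructions** gives the wording to be spoken to participants. They are to press "when you hear the infrequent ‘low−pitch tone’, and to make no response to the frequent ‘high−pitch tone". The common tone is called high and the rare tone low.
- **The Figure 3 legend** agrees with the script: "two types of sounds (high-pitched, 80% probability; low-pitched, 20% probability) are presented randomly".

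Formal acquisition sends the reader to Figure 3 for the operating procedure, and says that stimulus markers, EEG and button presses are recorded together. Analysis of EEG then averages target and standard epochs separately and takes the P300 as a peak at Cz between 300 and 600 ms.

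**The concern.** The script is meant to be spoken as printed, and the parameters section is the only place that gives tone frequencies, so a site building the task would naturally take the program from one and the instruction from the other. The two disagree on which pitch is rare.

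The oddball design needs the rare tone to be the one the participant attends and responds to. If some participants go by pitch and others by rarity, they perform different tasks under one label, and the coded target is no longer the attended tone for all of them. P300 is the trial's only neurophysiological outcome and is put forward as a possible biomarker, so an uncertain task would weaken the whole mechanistic part. An undocumented correction between the baseline and post-treatment recordings would also mix a change of task into the within-person change.

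**Working it through.** **Step 1. Pitch against probability.** 1000 Hz is lower than 2000 Hz.

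| Source | Low tone | High tone | Tone to press for |
|---|---|---|---|
| Stimulus presentation parameters | 80% (1000 Hz, standard) | 20% (2000 Hz, target) | 20% tone, high |
| Task instructions | infrequent | frequent | infrequent tone, low |
| Figure 3 legend | 20% | 80% | not stated |

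The low tone has probability 0.80 in the first row and 0.20 in the third; both cannot hold. The parameters and the script agree that the tone to detect is the rare one, and the parameters and the legend both put the rare tone at 20%. Only its pitch is in conflict.

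**Step 2. Which combinations fail.**

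- Program and script both take the rare tone as high: consistent.
- Program and script both take the rare tone as low: consistent.
- Program from the parameters section, script as printed: the rarity word in the script selects the 2000 Hz tone and the pitch word selects the 1000 Hz tone.

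The third combination is what the article gives when each section is used as written.

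**Step 3. Number of tones.** Inputs: run length 180 s ("The acquisition will last approximately 3 minutes"); interval 1.0 to 1.5 s ("inter-stimulus interval of 1.0–1.5 s, and total task duration of 3 minutes"); tone duration 50 to 100 ms.

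Tones = 180 / (interval + duration); rare = 0.20 × tones; common = 0.80 × tones.

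| Timing | Tones | Rare (20%) | Common (80%) |
|---|---|---|---|
| Shortest: 1.00 + 0.05 s | 171.4 | 34.3 | 137.1 |
| Middle: 1.25 + 0.075 s | 135.8 | 27.2 | 108.7 |
| Longest: 1.50 + 0.10 s | 112.5 | 22.5 | 90.0 |

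If the interval is read as onset to onset, tones = 180 / interval. This gives 120 to 180 tones, of which 24 to 36 are rare and 96 to 144 common.

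**Step 4. Consequence for a participant who goes by pitch.** Under the parameters section the low tone is the common one, so presses fall on about 109 of about 136 tones (range 90 to 137, or up to 144 onset to onset). With a consistent task they would fall on about 27 (range about 23 to 34, or up to 36).

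**The case against.** A reader might infer more than the text supports, in four ways.

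- **That participants are told to respond to the 80% tone.** They are not told this outright. The script says "Your task is to press the response button as quickly and accurately as possible when you hear the infrequent" tone, and only the pitch label attached to it leads to the common tone. Under the printed settings the instruction is self-conflicting, not simply wrong.
- **That the target P300 is undefined.** The target is defined by its role as the 20% tone, and the analysis section fixes the electrode, the window and the two measures. What is unsettled is the target's pitch.
- **That target epochs would be mislabelled.** Markers and key presses are recorded as separate synchronised streams. Epochs coded from stimulus markers follow the tone played, and a mismatch would show up as presses on standard trials. The risk is attention to the wrong tone.
- **That every recording of every participant is affected.** This requires the program to follow one section, the script the other, and every participant to put pitch above rarity. The 20 to 30 practice trials, meant to check comprehension and discrimination, could well expose the conflict first. The presentation file is not shown, so a slip confined to the article is equally consistent with the text.

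All four limits stand, and so does the outcome's modest rank: the Abstract lists P300 as secondary and the Discussion calls the EEG analysis exploratory. None of this removes the contradiction. The practice block may reveal it, but the article gives no rule for resolving it, and an experimenter who improvises departs from the standardised wording. Nor is this detail left to a fuller document: both versions are stated, and they disagree.

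**Conclusion.** The contradiction is certain from the text alone: the low tone is the 80% tone in the stimulus parameters and the 20% tone in the Figure 3 legend, and the script sides with the legend. Its effect is conditional. If the program follows the parameters and the script is read as printed, participants who go by pitch respond to about four tones in five instead of one in five, and P300 amplitude and latency from those recordings could not be read in the usual way. How many would do so cannot be known from the document, so the figure of about 109 presses is a worst case per recording, not an expected value. It assumes a 3-minute run at mid-range timing.

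The damage is confined to the P300. The HAMD-17 primary outcome, the other clinical scales, the safety data and the sample size do not depend on it.

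**What to change.** Choose one pitch for the 80% standard and the other for the 20% target. Either assignment removes the conflict. Then make these five items agree:

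1. the script in Task instructions;
2. the frequencies in Stimulus presentation parameters;
3. the Figure 3 legend;
4. the E-Prime file;
5. the EEG trigger codes.

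Make one test recording to confirm that the tone described as rare is played on about 20% of trials, carries the target marker and is the one that calls for a press. Keep the file and script unchanged across baseline (T0) and post-treatment (T1).

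The planned start was September 2025, so recording may already have begun. In that case, establish from the presentation file and logs which version each participant received, and document it. The pattern of button presses against markers will show whether anyone responded to the standard tone.

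The cost is a short text edit and one test recording, with no added burden on participants.

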### Safety outcomes

Safety and tolerability will be systematically assessed throughout the study. Treatment-emergent adverse events will be monitored using the TESS, a standardized clinician-rated instrument for evaluating the presence, frequency, and severity of stimulation-related side effects. Adverse events of interest include, but are not limited to, headache, dizziness, nausea, scalp discomfort, muscle twitching, and other potential symptoms associated with transcranial magnetic stimulation. All adverse events will be recorded at each treatment session and follow-up visit, and their severity and potential relationship to the intervention will be documented. For further details, please see **Supplementary Material S3**.

### Statistical analysis

#### Sample size

The sample size for this exploratory trial was determined *a priori* using G*Power software (version 3.1). An F-test was employed based on an effect size (Cohen’s d) of 0.38 by Chu et al. (2021). A total of 50 participants were required to achieve 80% statistical power at a two-sided alpha level of 0.05 (37). Anticipating an approximate dropout rate of 10%, the planned enrollment was at 56 participants.

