## Materials and methods

### Study design

This randomized, sham-controlled clinical trial was approved by the Ethics Committee of Wuxi Mental Health Center and prospectively registered in the Chinese Clinical Trial Registry (ChiCTR; official website: www.chictr.org.cn, Registration No.: ChiCTR2500109181). All procedures will adhere to the principles of the Declaration of Helsinki and the Guidelines for Good Clinical Practice (GCP). Reporting will follow the SPIRIT 2025 recommendations, and the completed SPIRIT checklist is available in **Supplementary Material S1**.

This trial will be conducted at Wuxi Mental Health Center between September 2025 and August 2027. The assessment and screening will be conducted by two practicing physicians from Wuxi Mental Health Center. Eligible participants will be randomly allocated (1:1) to receive either active sequential accelerated theta burst stimulation (aTBS; 3,600 pulses per session, 10 sessions total) or sham stimulation. Outcome measures will include the 17-item Hamilton Depression Rating Scale (HAMD-17) (24), Beck Depression Inventory (BDI-II) (25), Columbia Suicide Severity Rating Scale (C-SSRS) (26), Treatment Emergent Symptom Scale (TESS) (27) and event-related potential P300. All assessments will be administered at baseline (T0), immediately after the final stimulation session (T1), and at 2-week (T2) and 4-week (T3) follow-ups. A detailed flow diagram of the trial is shown in **Figure 1**, and the trial schedule is presented in **Table 1**.

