### Study outcomes

#### Primary outcome

The primary outcome is to compare the response rate of depressive symptoms between the active stimulation group and the sham stimulation group after intervention. The response rate is defined as a reduction of 50% or more in the HAMD-17 score compared with the baseline. Remission is defined as a HAMD-17 score of ≤ 7 (32).

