#### Analysis of clinical data

All statistical analyses will be conducted using SPSS version 26.0. Continuous variables will be presented as means ± standard deviations or medians (interquartile ranges), depending on distribution, and compared using independent samples t-tests or Mann-Whitney U tests, as appropriate. Categorical variables will be expressed as frequencies (%) and analyzed using Chi-square or Fisher’s exact tests. A repeated-measures analysis of variance (ANOVA) will be applied to evaluate longitudinal changes in each outcome, with group (active vs sham) as the between-subject factor and time (baseline, post-intervention, follow-up) as the within-subject factor. If the assumption of sphericity is violated according to Mauchly’s test, the Greenhouse-Geisser correction will be applied. Significant interactions will be followed by Bonferroni-adjusted simple-effects comparisons to determine between-group differences at each time point and within-group changes across time.

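### The stated 80% power with 50 patients does not apply to the primary comparison: the trial is sized by an unspecified F-test on a standardized mean difference, but the primary outcome is a response rate

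*Protocol article*

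**What the plan says.** The Sample size section states: "An F-test was employed based on an effect size (Cohen’s d) of 0.38". It continues: "A total of 50 participants were required to achieve 80% statistical power at a two-sided alpha level of 0.05". Enrolment is then inflated: "Anticipating an approximate dropout rate of 10%, the planned enrollment was at 56 participants". The section does not say which F-test was used, on which outcome, with how many measurements or at what correlation.

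Under Primary outcome the article says: "The primary outcome is to compare the response rate of depressive symptoms between the active stimulation group and the sham stimulation group after intervention". It adds: "The response rate is defined as a reduction of 50% or more in the HAMD-17 score compared with the baseline". The Abstract lists remission beside response as primary; both are binary.

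Under Analysis of clinical data: "Categorical variables will be expressed as frequencies (%) and analyzed using Chi-square or Fisher’s exact tests". The same paragraph plans a group-by-time repeated-measures ANOVA for longitudinal change in each outcome and lists three time levels. The Study design section schedules four assessments, T0 to T3. Allocation is 1:1.

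**The concern.** A power statement belongs to one test of one outcome at one assumed effect. Here the effect is a standardized mean difference and the test is an F-test, while the primary outcome is a proportion with its own tests. Turning d = 0.38 into a difference in response rates requires at least a sham response rate, and the article gives none.

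The figures also look inconsistent on their face. In a plain two-arm comparison, d = 0.38 is a modest effect that 50 patients cannot detect with 80% power.

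Readers will take the 80% as a property of the primary comparison. If its real power is much lower, a non-significant difference in response says little about whether the stimulation works, yet the published power would suggest otherwise.

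**Working it through.** **Inputs from the article.** d = 0.38, two-sided alpha 0.05, power 80%, N = 50 (25 per arm at 1:1), dropout 10%, enrolment 56 (28 per arm).

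**1. Dropout step.** 50 / (1 − 0.10) = 55.6, rounded up to 56. This reproduces.

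**2. N = 50 from the stated inputs alone.** For a two-group comparison at one time point, the noncentrality is d × √(n/2) with n per arm.
- n = 25: 0.38 × √12.5 = 1.34 on 48 degrees of freedom, power 26.1%.
- n = 28: power 28.7%.
- n = 110: 0.38 × √55 = 2.82, power 80.1%. At n = 109 it is 79.8%, so 110 per arm (220 in total) are needed.

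The one-way F-test with f = d/2 = 0.19 is the same test and gives the same answer. The stated 50 is not reproduced.

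**3. Can another F-test give about 50?** For a group-by-time interaction with m measurements and correlation r, the noncentrality is λ = f² × N × m / (1 − r), with m − 1 and (N − 2)(m − 1) degrees of freedom. With f = 0.19, f² = 0.0361. The values of r are assumptions.

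| m | r | N | λ | Power |
|---|---|---|---|---|
| 3 | 0.50 | 48 | 10.40 | 81.8% |
| 3 | 0.50 | 50 | 10.83 | 83.5% |
| 3 | 0.47 | 50 | 10.22 | 81.1% |
| 4 | 0.36 | 50 | 11.28 | 80.3% |
| 4 | 0.50 | 40 | 11.55 | 81.0% |

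A second route enters 0.38 as f, which equals d = 0.76, in a between-groups repeated-measures test with λ = f² × N × m / (1 + (m − 1)r). With m = 3, r = 0.8 and N = 50, λ = 0.1444 × 150 / 2.6 = 8.33 and power is 80.7%. Several sets of unstated settings therefore lead to about 50, and the article does not show which was used.

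**4. Power for the response rate.** The article assumes no rates. For the active arm I take 46%, the top of the 29–46% response range that the Introduction gives for conventional 10-Hz stimulation. The sham rates are my assumption. Power at 25 per arm is the sum of binomial probabilities over all outcome tables that the test rejects at two-sided 0.05.

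| Sham (assumed) | Active | Chi-square | Fisher |
|---|---|---|---|
| 15% | 46% | 70% | 56% |
| 20% | 46% | 52% | 39% |
| 25% | 46% | 36% | 25% |

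**5. Active rate needed for 80% power at 25 per arm.** With sham at 15, 20 or 25%, chi-square needs about 51, 57 or 62%. For sham at 20%, Fisher needs about 61%. The test must be named: 20% versus 57% gives 81% by chi-square but only 71% by Fisher.

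**The case against.** The strongest defence is that the article says F-test, and the only F-test it plans is the group-by-time repeated-measures ANOVA. With d = 0.38 correctly converted to f = 0.19, the three time levels listed there and an ordinary correlation of 0.47 to 0.5, the required number is 48 to 50. On that reading d, N and power agree. Test type, number of measurements and correlation are also details that a journal article may leave to the full protocol. The trial is called exploratory, and the limitations acknowledge a modest sample.

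Much of this stands. A reader might infer that the 80% is simply false and that the design has 26% power, or that d was typed into a field that expects f. The documents do not support either inference. The 26% belongs to a single-time-point two-group test that the article does not claim to have used, and an entry error cannot be shown from what is printed. That the calculation concerns the HAMD-17 score is likewise inferred from the use of d, because the section names no outcome.

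The defence has a limit of its own: it takes f = 0.19 as the size of the interaction. If the arms were equal at baseline and differed by 0.38 SD at both later visits, the interaction f would be 0.19 × √(2/9) = 0.090, and power at N = 50 with r = 0.5 would be about 26%.

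The defence also leaves the main point untouched. Even a correct interaction calculation gives no power for a chi-square or Fisher comparison of response rates. Calling the trial exploratory does not help, since the same paragraph claims 80%.

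**Conclusion.** The power statement is wrong as written for the primary outcome. It comes from a different kind of test on a different scale of effect, and no response rates are assumed from which power for the primary comparison could be derived.

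The size of the shortfall depends on rates that the article does not give. Under the assumptions shown, power runs from 25% to 70% according to sham rate and test. It reaches 80% only if active response is well above the article's own range for conventional stimulation.

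Separately, N = 50 cannot be reproduced from the printed inputs alone and depends on unstated repeated-measures settings. That is a gap in the reported basis for the number, not proof of a miscalculation.

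**What to change.** In the Sample size section, withdraw the 80% claim for the primary outcome. Replace it with a statement of what about 50 evaluable patients (25 per arm) can detect on HAMD-17 response, giving the assumed rate in each arm and the named test. For example, with an assumed 20% sham response, 80% power requires about 57% active response by chi-square or about 61% by Fisher's exact test. The investigators should supply and justify their own sham rate.

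If the F-test calculation is kept, label it as applying to the repeated-measures analysis of the score. Give the effect as f, and state which F-test was used, the number of measurements and the correlation.

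This costs one paragraph of wording and a less favourable stated power. It needs no extra patients and no change of primary outcome.
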